### Secondary outcomes

The secondary objectives are to compare between patients with the web-application support and patients with standard support:

The rate of adherence failure of adjuvant hormone therapy at 6 months, defined similarly as for primary endpoint.The adherence rate to adjuvant hormone therapy at 6 and 18 months, according to the MMSA8 adherence score, assessed 6 and 18 months after initiation of hormone therapy and the proportions of patients with “Low adherence” (score < 6), “medium adherence” (score ≤ 6 and < 8) and “high adherence” (score = 8), at each time. For patients categorized in “Low” or “Medium” adherence, the proportion of patients for whom the breast nurse and/or oncologist were warned.Pain scores according to the Brief Pain Inventory (BPI), at baseline and 18 months after the start of hormone therapy, and according to the numerical scale at each consultation at the center.Quality of life scores at inclusion, 6 months and 18 months, according to the EORTC QLQ-C30 self-questionnaire and the BR23 additional module.Anxiety and depression scores at baseline, 6 and 18 months, according to the HADS scale.Return to work and/or daily activities, through.
the proportion of patients who practice a professional activity 18 months after the hormone therapy start among patients of working age and in activity before the diagnosis of their breast cancer;Return to work and modalities (part-time, adaptation of the workstation…).
Patient satisfaction with their support during the first 18 months of hormone therapy, using a visual analog scale (VAS).Number of calls from patients to the hospital breast nurse over 18 months.Number of appointments proposed with the patient’s oncologist in case of low adherence.Number of appointments with the patient’s oncologist (excluding SCP) related to hormone therapy.

In addition, for patients in the experimental arm only, the appropriation, the ease of use and the degree of satisfaction of patients using the web-application, as well as the actions taken in case of poor adherence or non-adherence to hormone therapy will be evaluated with:

The number of connections to the web-application.The measurement of the usability of the web-application via the System Usability Scale (SUS).The number of patients who received practical advices to reduce the risk of forgetfulness.The number of contacts with the hospital breast nurse (via web-application or phone), with the aim of better understanding the difficulties encountered in terms of adherence and offering assistance to the patient.

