**Fig. 1 Fig1:**
[figure not shown]
A graduated immediate response adapted to the patient through the WEBAPPAC web-application

Besides this personalized monitoring, the web-application is intended to improve the management of ADRs induced by hormone therapy, by:

Providing health and dietary advices (physical activities and sports, practical advice, “take care of yourself” advice cards, cooking recipes, etc.)Providing information that will allow patients to apply symptomatic treatments without a prescription in close collaboration with their pharmacist (lubricant, level 1 analgesic, etc.)Referring patients to primary health care professionals (attending physician), organizations and structures adapted to their needs (sports educators, social workers, dieticians, patient associations, etc.).Alerting the nurse accompanying the patient on the breast cancer treatment pathway in the event of non-adherence with the hormone therapy treatment.

However, it is to notice that this device should not be considered as an emergency alert.

In this context, we implemented the WEBAPPAC study, herein presented. To our knowledge, this randomized study is the first one, to date, aiming to evaluate the effectiveness of using a web-application on adherence to adjuvant hormone therapy among breast cancer patients with breast cancer.

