#### Control arm: standard support only

During the end of active treatment consultation, the oncologist will prescribe the adjuvant hormone therapy treatment in accordance with multidisciplinary team decision and patient.

The SCP will be then given to the patient, presented as a personalized follow-up and medical monitoring program alternating with her general practitioner. The relay with the attending physician will be carried out. The oncologist will then receive patients in consultation at 6 and 18 months after the start of hormone therapy. The patient will be free to discuss any concerns she may have with her attending physician. Information on social and psychological support for the patient or her family will be provided by the breast nurses at the end-of-treatment consultation, supplemented by a brochure entitled “Preparing for Life After Treatment”.

The breast nurse who has accompanied the patient throughout her care will remain available by phone or email if necessary.

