### Study assessments

The overview of study assessments and procedures is detailed in Table 2.

**Table 2 Tab2:** Overview of study assessments in the WEBAPPAC study

TIME Point	Before inclusion	Inclusion and randomisation ^a^	Day 15^b^	6 Week^b^	3-months^b^	6-months^a^	18-months ^a^
		Visit 1				Visit 2	Visit 3
Informed consent	•	•^a^					
**Training of the patient in the Web application**		**•** ^**b**^					
**Medical examination** (medical history, weight, height, vital parameters)		**•** ^**a**^					
**Quality of life self-report questionnaires (EORTC QLQ C30; and QLQ BR23)**		**•** ^**a**^				**•** ^**a**^	**•** ^**a**^
**Anxiety and Depression Questionnaire (HADS)**		**•** ^**a**^				**•** ^**a**^	**•** ^**a**^
**Assessment of pain using the Visual Analogue Scale (VAS)**				**•** ^**b**^	**•** ^**b**^	**•** ^**a**^	**•** ^**a**^
**Pain score (BPI)**		**•** ^**a**^					**•** ^**a**^
**Morisky Medication Adherence Scale (MMAS8)**				**•** ^**b**^	**•** ^**b**^	**•** ^**a**^	**•** ^**a**^
**Measurement of user experience (self-questionnaire (SUS))**							**•** ^**b**^
**Phone call** to ensure that there are no technical difficulties.			**•** ^**b**^				
**Evaluation of adherence to hormone therapy treatment by traceability of delivery, adherence notebook and patient declaration**						**•** ^**a**^	**•** ^**a**^
**Return to work and/or daily activities**					**•** ^**b**^	**•** ^**a**^	**•** ^**a**^
**Number of calls to the breast nurse**						**•** ^**a**^	**•** ^**a**^
**Patient satisfaction with 18-month follow-up**							**•** ^**a**^

^a^ During consultation at the Center with the medical oncologist in both arms

^b^ Only for the experimental arm (WEBAPPAC), at home

At inclusion, patients will be asked to complete the following self-questionnaires: EORTC QLQ-C30 and BR23, HADS, and BPI.

During their participation, assessments will be realized 6 and 18 months after the initiation of hormone therapy as follows:

Adherence to hormone therapy (MMAS8, adherence notebook, dispensation, patient report).Quality of life (QLQ-C30 and BR23 self-questionnaires).Anxiety and depression level (HADS self-questionnaire).Return to work and/or daily activities.Pain level (VAS at 6 and 18 months, and BPI at 18 months only).Patient follow-up satisfaction (VAS, at 18 months only).

In addition, patients in the experimental arm will be asked to fulfill the following assessments:

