At 6 weeks and 3 months after the hormone therapy start using the WEBAPPAC web-application:Pain level (VAS).Adherence to hormone therapy (MMAS8).Return to work and/or daily activities, at 3 months only.At 18 months, measurement of the user experience of the web-application via the System Usability Scale (SUS) self-questionnaire.

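### The between-arm test of the proportion warned among Low or Medium adherers is not a randomised comparison, and part of its numerator is an app function

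*Protocol article*

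**What the plan says.** The Secondary outcomes section of the protocol article opens its main list with "The secondary objectives are to compare between patients with the web-application support and patients with standard support". One bullet in that list covers adherence by MMAS8 score at 6 and 18 months. Its last sentence adds, "For patients categorized in “Low” or “Medium” adherence", "the proportion of patients for whom the breast nurse and/or oncologist were warned". The same section has a separate list for the experimental arm only, whose stated scope includes actions taken when adherence is poor. The warned proportion is not in that list and is nowhere marked as descriptive.

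The Statistical analyses section compares secondary endpoints between groups by chi-squared test (Fisher's exact if needed) for qualitative variables, at 5% for each analysis.

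On how staff come to be warned:
- The WEBAPPAC web-application section lists among the app's functions "Alerting the nurse accompanying the patient on the breast cancer treatment pathway in the event of non-adherence with the hormone therapy treatment".
- Under standard support, the breast nurse "will remain available by phone or email if necessary", and the oncologist sees the patient at 6 and 18 months.
- Table 2 places the 6- and 18-month MMAS8 "During consultation at the Center with the medical oncologist in both arms".
- Only the app arm also completes the MMAS8 "At 6 weeks and 3 months after the hormone therapy start using the WEBAPPAC web-application".

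**The concern.** There are two separate difficulties.

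The first is the denominator. Low or Medium status is an MMAS8 score below 8 after randomisation. It is itself a compared outcome in the same bullet, and its Low category at 18 months is a component of the primary endpoint. If the app works, it changes which patients remain in the subgroup. The Low or Medium patients in the two arms need not then be alike, and the intent-to-treat statement cannot repair a comparison confined to them.

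The second is the numerator. One of the routes by which staff are warned is supplied by the intervention and is absent from standard support. A higher proportion in the app arm may show no more than that the alert was delivered.

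What is at stake is interpretation: a p-value below 0.05 on this item could be reported as a randomised treatment effect when it is not one.

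**Working it through.** **The plan's own figure.** The article states no figure for this outcome, so the sample size is checked only to fix the numbers available. With 20% v 10%, two-sided 5%, 80% power and pooled variance under the null:

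n = [1.960·√(2·0.15·0.85) + 0.8416·√(0.20·0.80 + 0.10·0.90)]² / 0.10² = (0.990 + 0.421)² / 0.01 ≈ 199 per arm.

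This matches the stated 199 (398 in total; 219 per arm enrolled).

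**Inputs that must be assumed.** The article gives neither a Low or Medium share for this population nor any warned rate. Three shares are tried: 20% (the assumed control failure rate, which is a composite and not the Low or Medium share), 37% (poor adherence in a cited cohort) and 59% (100% minus the 41% adherent in another cited study). All warned rates below are assumptions.

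**A. Numerator effect with identical adherence.** Take 199 evaluable patients per arm and the same share in both, giving 40, 74 or 117 patients per arm in the subgroup. The probability that a two-sided 5% chi-squared test is significant is obtained by enumerating all pairs of binomial counts and summing the probability where the statistic exceeds 3.841.

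| Warned, control v app | 40 per arm | 74 per arm | 117 per arm |
|---|---|---|---|
| 30% v 30% | 5% | 5% | 5% |
| 30% v 50% | 46% | 72% | 89% |
| 30% v 60% | 80% | 97% | >99% |
| 30% v 90% | >99% | >99% | >99% |
| 80% v 95% | 57% | 82% | 95% |

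Single-table examples use 44 per arm (20% of 219 = 43.8). For 42 v 35 warned (95% v 80%), Fisher p = 0.049, uncorrected chi-squared p = 0.024 and continuity-corrected p = 0.053, so the result is borderline. For 42 v 31 (95% v 70%), Fisher p = 0.003.

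**B. Denominator effect with identical staff behaviour.** Suppose control has 10% severe and 50% mild non-adherers, the app halves the mild group, and staff warn 90% of severe and 40% of mild cases in both arms.
- Control: (0.10·0.9 + 0.50·0.4) / 0.60 = 0.29 / 0.60 = 48.3%.
- App: (0.10·0.9 + 0.25·0.4) / 0.35 = 0.19 / 0.35 = 54.3%.

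With 219 per arm the subgroups hold about 131 and 77 patients. By normal approximation, a two-sided 5% test is significant about 13% of the time.

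The direction is not fixed. If half of the non-adherers have a 60% chance and half a 20% chance of being warned, and the app makes half of the first type adherent, control shows 0.5·0.6 + 0.5·0.2 = 40%. The app arm shows (0.25·0.6 + 0.5·0.2) / 0.75 = 33%.

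**C. All-randomised denominator, using the rates in B.** Low or Medium and not warned: control 0.10·0.1 + 0.50·0.6 = 31%; app 0.10·0.1 + 0.25·0.6 = 16%. Staff behaviour is unchanged, so the whole movement comes from adherence.

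**The case against.** The best defence is that this is a process measure. It asks whether staff learned of poorly adherent patients, and a process measure may properly differ when adherence does not. Adherence is compared separately, in the primary endpoint, in failure at 6 months and in the Low, Medium and High proportions. The article nowhere offers the warned proportion as evidence of better adherence. This stands: significance with identical adherence is not a defect in itself.

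It also stands that the numerator is only partly built into the app. The article describes an alert to the nurse for non-adherence. It describes no alert to the oncologist and none triggered at Medium adherence, and control patients can reach the nurse and do see the oncologist.

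A reader might infer from Table 2 that the oncologist is always aware of the score, so that the outcome tends to 100% in both arms. The documents do not support that. The footnote places the assessment at the consultation but does not say that the oncologist reads or scores the questionnaire, and app-arm patients are reminded to complete theirs a week beforehand.

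Finally, the selection effect illustrated is modest and all its rates are assumed.

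What the defence does not answer is that the article puts the item under comparison and sends it to a 5% test within an outcome-defined subgroup. That is a stated choice, not a detail left to an unseen analysis plan.

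**Conclusion.** The concern holds in a limited form and is minor. As written, the test compares groups that randomisation does not protect, on a numerator that the intervention partly supplies. A significant result may reflect delivery of the app or a changed case mix and should not be read as a randomised treatment effect.

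The size cannot be fixed from the article. Under the assumed rates, selection alone shifts the proportion by 6 to 7 points in either direction, while a real difference in warning would often be significant without any difference in adherence.

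A reader might go further and infer that the item is wholly an artefact or carries no information about care. Neither follows: the numerator has routes in both arms, and the proportion remains a useful description of process. The primary endpoint, its test and the sample size are unaffected.

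**What to change.** Report the proportion descriptively in each arm, as n/N with a 95% CI, label it a process measure, and drop the between-arm test. Apply the same meaning of warned in both arms. Keeping both arms is better than moving the item to the experimental-arm-only list, which would lose the control benchmark.

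If a comparison is kept, use all randomised patients as the denominator: Low or Medium adherence and no staff member warned, by arm. State beside it that the measure combines adherence with warning, so it cannot show by itself whether warning improved (part C of the working).

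The cost is a wording change and one fewer tested secondary outcome.

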## Background

### Breast cancer, hormone therapy, adverse effects and adherence

With 58,459 new cases yearly in France, breast cancer remains the most common cancer in women [1]. Thanks to breast cancer screening campaigns and improved treatments, the 5-year survival rate is 88% [1]. The treatment of non-metastatic breast cancer is mainly based on surgery, with or without chemotherapy, radiotherapy and/or hormone therapy.

Hormone-dependent breast cancer can relapse long after treatment has ended. Approximately 80% of patients have hormone receptor-positive (HR+) tumors [2]. In France, more than 40,000 new breast cancer patients are yearly treated with adjuvant hormone therapy. Hormone therapy is an anti-cancer treatment with an indirect mechanism of action through the inactivation of estrogen. Tamoxifen, as well as aromatase inhibitors (AI), are used for patients whose tumor tissue immunochemistry identifies positive estrogen receptors and/or positive progesterone receptors (ER+/PR+).

To reduce the risk of recurrence in women with HR + breast cancer, hormone therapy is prescribed for at least 5 years. Tamoxifen has become the gold standard of treatment before menopause while aromatase inhibitors have become established after menopause. Randomized trials and meta-analyses have shown that these hormone therapies lead to a gain in relapse-free and overall survivals [3–5]. Furthermore, as the duration of treatment is fundamental to ensure its effectiveness, hormone therapy is nowadays prescribed between 5 and 10 years depending on the indication [6, 7].

Hormone therapy is responsible for adverse drug reactions (ADRs) that usually occur between one and three months after the start of treatment. These ADRs are related to the absence of estrogen impregnation and vary according to the type of medication used (Tamoxifen® or anti-Aromatase/GnRH analogues) and to the patient’s menopausal status. They are related and intertwined with the menopausal effects in women, whatever the menopause was before diagnosis or occurred during chemotherapy.

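### Pain schedule: the scale due at every consultation is not scheduled at inclusion, and the BPI is not repeated between inclusion and month 18

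*Protocol article*

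**What the plan says.** The protocol article describes pain measurement in four places.

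- **Secondary outcomes** lists pain among the outcomes to be compared between arms. One instrument is "Pain scores according to the Brief Pain Inventory (BPI), at baseline and 18 months after the start of hormone therapy". The other is a pain score "according to the numerical scale at each consultation at the center".
- **Study assessments, Table 2** heads the inclusion column as Visit 1. Its footnote a describes the assessments so marked as made at a consultation at the centre with the oncologist in both arms. The VAS row is empty at inclusion. It is marked at 6 weeks and 3 months with footnote b ("Only for the experimental arm (WEBAPPAC), at home") and at 6 and 18 months for both arms. The BPI row is marked at inclusion and month 18.
- **Study assessments, text** agrees with the table. For inclusion: "At inclusion, patients will be asked to complete the following self-questionnaires: EORTC QLQ-C30 and BR23, HADS, and BPI". For follow-up in both arms: "Pain level (VAS at 6 and 18 months, and BPI at 18 months only". For the experimental arm: "At 6 weeks and 3 months after the hormone therapy start using the WEBAPPAC web-application:Pain level (VAS".
- **Background** says that hormone therapy causes "adverse drug reactions (ADRs) that usually occur between one and three months after the start of treatment".

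Under Statistical analyses, quantitative secondary endpoints are compared by a Student's test or a Wilcoxon Mann Whitney test. Adjustment for baseline is not mentioned.

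**The concern.** Managing side effects is a stated aim of the application, and joint pain is the first side effect listed. The two instruments named for the pain outcome should therefore be scheduled so that they can inform that aim. Three features work against this.

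1. The outcome definition and the assessment schedule disagree about inclusion. If sites follow Table 2, no baseline VAS is collected, and it cannot be recovered later. Patients arrive after cancer treatment, so some will already have pain.
2. The BPI, which also records the impact of pain on daily life, has a single post-baseline point. That point is far from the period in which the Background expects side effects to arise.
3. Pain in that early period is recorded in one arm only.

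There is also a naming problem. Secondary outcomes speaks of a numerical scale, while the abstract, Study assessments and Assessment tools speak of a VAS. These are different response formats, and the outcome should rest on one.

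**Working it through.** **Schedule side by side** (from Table 2, its footnotes and the text of Study assessments; the QLQ-C30 pain scale from Assessment tools, Quality of life):

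| Time | VAS | BPI | QLQ-C30 pain scale |
|---|---|---|---|
| Inclusion (Visit 1) | none | both arms | both arms |
| 6 weeks | application arm only | none | none |
| 3 months | application arm only | none | none |
| Month 6 (Visit 2) | both arms | none | both arms |
| Month 18 (Visit 3) | both arms | both arms | both arms |

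**Contradiction.** Table 2 has three centre consultations. Secondary outcomes implies the scale at all 3; the schedule gives it at 2. The empty cell is unlikely to be a table-reading fault, because the inclusion list in the text omits the VAS as well.

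**Distance from usual onset.** Onset is put at 1 to 3 months. The first post-baseline pain measure common to both arms is at month 6, which is 6 − 3 = 3 months after that window closes. The first post-baseline BPI is at month 18, which is 18 − 3 = 15 months after. Of the two early VAS assessments, none is taken in the control arm.

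**Does stopping of treatment distort month 18 materially?** The documents give no pain scores, so this is an illustration on assumed values: mean pain 4 of 10 on treatment, 2 to 3 of 10 after stopping, no application effect on pain, and the planning failure rates of 20% and 10% taken as the shares off treatment.

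Mean at month 18 = P(on) × pain on + P(off) × pain off.

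- Off value 2: control 0.8 × 4 + 0.2 × 2 = 3.60; application 0.9 × 4 + 0.1 × 2 = 3.80; difference +0.20.
- Off value 2.5: 3.70 and 3.85; difference +0.15.
- Off value 3: 3.80 and 3.90; difference +0.10.

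For scale, take the plan's 199 evaluable patients per arm. That figure reproduces with a pooled two-proportion z-test, 20% v 10%, two-sided 5%, 80% power: [1.96 × √(2 × 0.15 × 0.85) + 0.8416 × √(0.2 × 0.8 + 0.1 × 0.9)]² / 0.1² ≈ 199. With an assumed SD of 2 to 3 points, the difference in means detectable at 80% power is (1.96 + 0.8416) × SD × √(2/199) ≈ 0.28 × SD, or 0.56 to 0.84 points. The illustrated shift of 0.1 to 0.2 is well below this.

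**What a baseline value adds.** Randomisation already makes an unadjusted VAS comparison unbiased in expectation. Adjustment for baseline multiplies the residual variance by about 1 − r², where r is the correlation between baseline and follow-up. The documents do not give r, so the gain cannot be quantified here.

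**The case against.** The strongest reply is that pain is adequately covered already, and much of it stands. The BPI is completed at inclusion in both arms and rates maximum, minimum, average and current pain from 0 to 10, so pre-treatment pain is on record. The QLQ-C30 pain scale is given at inclusion, 6 and 18 months in both arms, so a baseline-plus-month-6 comparison exists on a third instrument. The early VAS is delivered through the application, and standard follow-up has visits only at 6 and 18 months, so leaving it out of the control arm is a defensible way to keep the comparator standard. The remedy below does not fill that window either.

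A reader might infer three stronger things, none of which the documents support.

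- *That there is no BPI before month 18.* There is one at inclusion; what is missing is any between inclusion and month 18.
- *That the month-18 comparison is invalid, because women who stopped on account of pain are by then off the drug.* The documents do not say how many stop because of pain, and some may restart. The failure composite also counts low Morisky scores and one-month gaps, so not every failure is off treatment. Patients who withdraw remain in follow-up unless they decline. Pain regardless of treatment status is a legitimate intention-to-treat (treatment-policy) comparison.
- *That month 6 escapes this problem.* The Background cites 20% discontinuation within the first year in one study, so early stopping can affect month 6 too. Making it the main time point would be a trade-off, not a correction.

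The reply does not remove the conflict over inclusion. Nor does it explain why the BPI is omitted at a visit where the QLQ-C30, BR23 and HADS are all repeated.

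**Conclusion.** The point holds as a scheduling fault in one secondary outcome. Secondary outcomes and Table 2 cannot both be followed at Visit 1, the scale carries two names, and the BPI has no assessment between inclusion and month 18. After baseline the arms can be compared on pain only at months 6 and 18, and on the BPI only at month 18.

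The consequence is limited: a loss of baseline adjustment on the VAS and of a month-6 comparison on the BPI, partly offset by the baseline BPI and the QLQ-C30 pain scale. The primary endpoint and the sample size are unaffected. The possible shift from differential stopping, 0.1 to 0.2 points on a 10-point scale, rests wholly on assumed values and does not show material distortion. It would be too strong to say that the trial cannot separate failure to relieve pain from keeping more women on treatment. Adherence and discontinuation are recorded in both arms at 6 and 18 months, so the two can at least be described together, although the month-18 pain difference alone does not isolate the application's effect on side-effect management.

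**What to change.** 1. Reconcile Secondary outcomes with Table 2 by adding the VAS at Visit 1 in both arms, in the table and in the inclusion list.
2. Use one name and one response format for the scale throughout.
3. Add the short BPI at Visit 2 (month 6) in both arms.
4. Compare pain at 6 and 18 months with adjustment for the baseline value of the same instrument. For any patient already included without a baseline VAS, state in advance which baseline BPI intensity item serves as the covariate.
5. Keep month 18 as an intention-to-treat (treatment-policy) result. Pain by on/off hormone-therapy status may be shown descriptively only, because that status arises after randomisation and the application is meant to change it.
6. State that the 6-week and 3-month VAS describes the application arm only.

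The cost is one VAS and one short questionnaire at visits that already take place, plus the edits to Table 2 and the text. The downside is slightly more questionnaire burden, mainly at month 6. The early window stays without a control-arm measure, and the report should say so.
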